#### Functional connectivity modifications

In order to assess if behavioral modifications will be accompanied by an underlying change in the connectivity of the TMS target, we will statistically compare pre and post connectivity estimates by means of a 2 × 2 mixed Analyses of Variance (ANOVA), with the two factors representing respectively the Group (active vs. sham, between-subjects) and the Time (baseline vs. post-treatment, within-subject). The graph theory framework will be used to verify our hypothesis that the individualized stimulation protocol will result in enhanced connectivity between the parietal TMS target and the networks' overlap map (i.e., the conjunction between the neural regions involved in body schema representation and in implicit behavioral tendencies). In more detail, we expect the active group to show increased connectivity, i.e., a lower path length, in the post-treatment compared to the pre-treatment scan between these two sites, where the path length is measured as the inverse of the connectivity strength. At the same time, we expect that the broader network of regions involved in both body schema and implicit behaviors will show greater global efficiency, which reflects enhanced integration between distant nodes and is mathematically computed as the inverse of the averaged path lengths between all pairs of nodes, such as that short paths between all pairs of nodes translate in greater global efficiency of the overall network. We expect increased global efficiency as a result of the repeated activation of the targeted regions by means of the stimulation. Finally, in consideration of the fact that the TMS-induced effects on the functional connectivity can extend beyond the stimulation target (Beynel et al., 2020), we will address potential changes in the overall connectivity of the brain. In particular, we will test if the brain connectome might benefit from a functional re-arrangement that might lead to a concomitant increase in both global (every region can be linked by means of a short few paths) and local (regions cluster together into specialized modules) efficiency. This property is known as small worldness, which the literature suggests being decreased in AN patients compared to controls (Geisler et al., 2020). Small-worldness reflects hence the ratio between the average path length of a network and its clustering coefficient (i.e., a measure of the tendency of neighboring nodes to form triangular triples and thus to display high local efficiency).

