### Participants and recruitment

Participants will be recruited from the Eating Disorder Center of the Hospital of Padova, Italy. All eligible female patients followed at the center will be invited to take part in the study, as an adjunct to TAU, in agreement with their treating clinician. Recruitment will be limited to female patients due to the low number of male patients accessing the center and to minimize potential gender-related confounding factors.

Inclusion criteria will be: (1) current diagnosis of AN according to DSM-5 criteria; (2) age ≥18 years; (3) unsuccessful completion of at least one 3-month course of outpatient treatment; (4) illness duration of at least 1 year, and (5) female gender.

Exclusion criteria will be: (1) Presence of significant neurological comorbidities or severe/unstable systemic diseases, (2) Diastolic blood pressure < 60 mmHg or heart rate < 60 bpm, (3) diagnosis of psychosis or substance abuse disorders, (4) history of hypomanic/manic episodes, (5) Current suicidal ideation, (6) known contraindications to TMS as assessed with the TMS safety checklist (Rossi et al., 2021), including epilepsy, head trauma with loss of consciousness, severe/frequent headaches, cochlear implants, pacemakers, pregnancy, metallic implants, implanted neurostimulators; and (7) known contraindications to MRI, as assessed with the Hospital of Padova MRI safety checklist (Mod. Rev. 2, 16/05/2023), including presence of medical devices or metallic material, history of surgery or significant physical trauma, claustrophobia, pregnancy.

*A priori* power analysis conducted with G^*^Power (Faul et al., 2007) indicated that 28 participants are required to detect a significant group (2) × time (3) interaction assuming a medium effect size (Cohen's *f* = 0.25), statistical power of 1–β = 0.80, and significance level α = 0.05, with a correlation among repeated measures of *r* = 0.5. To account for potential dropouts, the sample size will be increased by 20%, resulting in a final target enrollment of 34 participants.

The study has been approved by the Ethics Committee of the Hospital of Padova (protocol number 6168/EST/25) and registered on ClinicalTrials.gov (registration number: NCT07106645). Written informed consent will be obtained from all participants prior to enrollment. Participants will be informed that their involvement is voluntary and that they may withdraw at any time without any consequences for their ongoing treatment.

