### Outcome measures

In the week prior to the start of treatment, all participants will undergo a baseline assessment consisting of: (1) an independent clinical evaluation conducted by a psychiatrist not involved in the study; (2) self-administered clinical scales; (3) an MRI scan including both structural and functional sequences; and (4) an assessment battery comprising behavioral and neurocognitive tasks designed to evaluate implicit body representation, food-related processing, and broader cognitive functions. The post-treatment assessment will take place in the week immediately following the final TMS session and will include the same components as the baseline assessment. Finally, a follow-up evaluation will be conducted 4 months after the post-treatment assessment, repeating all baseline and post-treatment measures, with the exception of the MRI scan. See Figure 2 for a graphical description of the procedure.

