#### Clinical, behavioral and cognitive outcomes

Analyses will be conducted according to the intention-to-treat principle. For each outcome, longitudinal changes will be evaluated using linear mixed-effects models (LMMs) with fixed factors of Group (active vs. sham), Time (baseline, post-treatment, 4-month follow-up), and their interaction (Group × Time). Random intercepts for participants will be included to account for within-subject correlations across repeated measurements. Effect sizes and 95% confidence intervals will be reported alongside p-values.

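### The connectivity outcomes are compared on raw change scores; adjusting for the baseline scan would estimate the arm difference more precisely at no cost

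*Protocol article*

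**What the plan says.** In the protocol article, Analyses, Functional connectivity modifications, the plan is that "we will statistically compare pre and post connectivity estimates by means of a 2 × 2 mixed Analyses of Variance (ANOVA"). The factors are Group (active or sham) and "the Time (baseline vs. post-treatment, within-subject"). The outcomes there are the path length between the stimulated target and the networks' overlap map, the global efficiency of that network, and whole-brain small-worldness.

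Only two scans exist. Under Outcome measures, "The post-treatment assessment will take place in the week immediately following the final TMS session", and the 4-month visit is described as "repeating all baseline and post-treatment measures, with the exception of the MRI scan".

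The clinical, behavioral and cognitive outcomes have their own subsection. It says "Analyses will be conducted according to the intention-to-treat principle" and uses linear mixed models over three time points.

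The sample size, under Participants and recruitment, belongs to another test: "28 participants are required to detect a significant group (2) × time (3) interaction", with "Cohen's *f* = 0.25), statistical power of 1–β = 0.80, and significance level α = 0.05" and a correlation of 0.5. It continues: "To account for potential dropouts, the sample size will be increased by 20%, resulting in a final target enrollment of 34 participants".

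**The concern.** With two time levels, the Group × Time F test in a mixed ANOVA is the square of the two-sample t test on post minus pre. Randomisation makes the arms equal at baseline in expectation, so subtracting the whole baseline value removes more than the correlation justifies and adds noise whenever r is below 1. Regression on baseline subtracts only the part that predicts the second scan.

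The second issue is missing scans. Suppose the chance of losing the T1 scan depends on baseline connectivity, and does so differently by arm. The patients with both scans then differ between arms at baseline. Regression to the mean turns that imbalance into an apparent difference in change. A baseline-adjusted comparison removes it when loss depends only on arm and baseline.

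At stake is the precision, and possibly the accuracy, of the comparison that the Abstract presents as the test of whether stimulation strengthens body-schema circuits.

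**Working it through.** **1. The plan's own figure.** The G*Power form for the within-between interaction is λ = f²·N·m/(1 − r), with df (g − 1)(m − 1) and (N − g)(m − 1). Sphericity is assumed. With f = 0.25, r = 0.5, g = 2 and m = 3:

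- N = 28: λ = 0.0625 × 28 × 3/0.5 = 10.5, df 2 and 52, power 0.812.
- N = 26: power 0.778.

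The stated 28 is therefore reproduced. Then 28 × 1.2 = 33.6, rounded up to 34. The allowance is 34 − 28 = 6 patients, and 6/34 = 17.6%.

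**2. The connectivity test as planned.** Set m = 2 and borrow f and r, because the article gives none for connectivity. At r = 0.5:

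- 34 pairs: λ = 0.0625 × 34 × 2/0.5 = 8.5, power 0.807.
- 28 pairs: λ = 7.0, df 1 and 26, power 0.721.

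**3. Variance with baseline adjustment.** Take equal variance σ² at both scans, and n pairs per arm.

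- Change scores: 2 × 2σ²(1 − r)/n.
- Baseline-adjusted, large sample: 2 × σ²(1 − r²)/n.
- Ratio: (1 − r²)/[2(1 − r)] = (1 + r)/2, which is 0.65, 0.75 and 0.85 at r = 0.3, 0.5 and 0.7.

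Equal variances are not needed for the direction of the result. With standard deviations σ₀ and σ₁, the per-patient change variance exceeds the adjusted one by (σ₀ − rσ₁)², which is never negative.

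**4. Power with 28 complete pairs.** Divide λ by the ratio and spend one more degree of freedom (1 and 25).

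| r | λ, change | Power, change | λ, adjusted | Power, adjusted |
|---|---|---|---|---|
| 0.3 | 5.00 | 0.577 | 5.00/0.65 = 7.69 | 0.760 |
| 0.5 | 7.00 | 0.721 | 7.00/0.75 = 9.33 | 0.835 |
| 0.7 | 11.67 | 0.908 | 11.67/0.85 = 13.73 | 0.945 |

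These are large-sample ratios. In simulation at r = 0.5 with about 20% loss, the realised ratio was about 0.81 to 0.85 rather than 0.75. With 27 pairs that gives adjusted power of roughly 0.78 to 0.82, against 0.704 for change scores.

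**5. Patients without a second scan.** Compare 14 complete pairs per arm with the same 14 plus 3 baseline-only patients per arm. In the model with equal baseline means, the variance of the T1 arm difference (in σ²) is 0.130, 0.107 and 0.073 at r = 0.3, 0.5 and 0.7. It is identical with and without the baseline-only patients, because they inform only the common baseline mean. An unconstrained mixed model with the same 6 patients raises the effective number from 28 to about 29.3 at r = 0.5, and power from 0.72 to about 0.74.

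**6. Possible bias.** If the completers' baselines differ between arms by D, the expected change scores differ by (1 − r)·D in size with no true effect. The simulations used 17 per arm, no effect and about 20% loss. The loss mechanisms are assumed, since the article gives none.

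| Loss mechanism (log-odds slope of 1 per SD) | Change-score bias in SD, at r = 0.3, 0.5, 0.7 |
|---|---|
| Opposite directions by arm | about 0.25, 0.18, 0.11 |
| One arm only | 0.13, 0.09, 0.05 |
| Same in both arms | about 0 |

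The first row agrees with the formula: 0.25/0.7 gives D of about 0.36, and 0.5 × 0.36 = 0.18 and 0.3 × 0.36 = 0.11. The baseline-adjusted estimate stayed within 0.007 SD of zero.

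**The case against.** The strongest case against is that a change-score comparison is valid and conventional, and that connectivity is neither a primary outcome nor one of the secondary outcomes listed at the end of the Introduction. That stands, and it limits the severity. It does not remove the efficiency gain.

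Three stronger readings are tempting, and the document does not support them.

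- **That the ANOVA discards randomised patients whom another model would keep.** It does use only complete pairs, unlike the mixed models for the clinical outcomes. However, the proposed adjustment recovers none of these patients, and an unconstrained mixed model gains almost nothing. The limit comes from having two scans, not from choosing ANOVA. The intention-to-treat sentence stands in the subsection on clinical, behavioral and cognitive outcomes, so there is no contradiction. A rule for missing scans may stand in the full protocol or analysis plan.
- **That about 20% of patients cannot be scored.** The 20% is an increase on 28, which allows a 17.6% loss of 34, and no time point is attached to it. A patient lost between T1 and the 4-month visit still has both scans. Within the plan's allowance, 17.6% is therefore an upper bound on dropout before T1, although unusable scans could add to it.
- **That the comparison is underpowered.** The article claims no power for connectivity and gives no effect size for it. With 28 pairs and f = 0.25, power runs from 0.58 to 0.91 as r goes from 0.3 to 0.7. The fall from 0.81 to 0.72 at the same N = 28 comes from two time points instead of three.

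The objection that the bias figures rest on an assumed mechanism also stands. Nothing in the article links dropout to baseline connectivity.

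**Conclusion.** The point holds as an efficiency point of low severity. The planned interaction is a raw change-score test, and adjusting for a baseline scan that is collected anyway cuts the large-sample variance of the arm difference by 25% at r = 0.5 (35% at r = 0.3, 15% at r = 0.7). The power gain is largest when the two scans correlate weakly and small when r is 0.7. It rests on f and r borrowed from the clinical sample-size calculation, equal variances at the two scans and a large-sample ratio, so the realised gain will be somewhat smaller.

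The bias is a possibility, not a demonstrated defect. It needs loss of the second scan to depend on baseline connectivity differently by arm, and it vanishes when the dependence is the same in both arms. Adjustment protects only against loss that depends on arm and baseline.

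**What to change.** In Functional connectivity modifications, replace the 2 × 2 mixed ANOVA. For each connectivity measure, regress the post-treatment value on arm and the baseline value of the same measure, or fit the equivalent two-time-point model with baseline means constrained equal across arms. Report the adjusted between-arm difference at T1 with its 95% CI, and the number of complete pairs in each arm. State that the arm difference rests on patients with both scans.

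The cost is a change of analysis wording. No new scans, data or patients are needed.

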
## Discussion

The present protocol introduces an attempt to broaden the application of TMS in AN by moving beyond the prefrontal cortex, which has so far represented the predominant neuromodulation target (Bahadori et al., 2025). Here, stimulation is directed to the PPC with the aim of modulating neural systems involved in body representation and in the emergence of rigid, implicitly driven eating behaviors, two domains that are central to the disorder and often resistant to conventional treatments. Target localization is individualized on the basis of resting-state connectivity, identifying posterior parietal nodes with the strongest co-activation within circuits relevant to body representation and cue-triggered eating behaviors. This approach provides a neurobiologically informed rationale for intervention and aligns with the principles of precision psychiatry, by tailoring stimulation to networks relevant in the maintenance of specific symptom dimensions (Williams et al., 2024). The outcome assessment is designed to span multiple levels. Core clinical outcomes include body weight and BMI, menstrual status, and changes in eating disorder psychopathology. Broader psychopathological dimensions such as anxiety and depression are also systematically evaluated. In addition, the study places particular emphasis on implicit processes related to body representation and food-related behavior, domains that are less accessible through self-report measures. To this end, the protocol incorporates experimental paradigms delivered through virtual reality and mobile applications, allowing the capture of distortions in body representation and automatic responses that are rarely addressed in routine clinical assessments. Together, these multimodal measures aim to provide a more comprehensive picture of treatment effects, bridging clinical symptomatology with underlying cognitive processes and neural mechanisms.

This protocol also faces important challenges, both clinical and methodological, that deserve careful attention. First, adherence and engagement can be challenging in AN, where ambivalence for treatment and strong need for control are common. Qualitative accounts embedded in an rTMS feasibility program describe rTMS as acceptable yet time-consuming, with mixed reactions about “brain-directed” interventions and their impact on agency, underscoring the importance of careful consent, expectation management, and qualitative feedback throughout the trial (Dalton et al., 2022).

Second, the PPC is a novel and largely unexplored stimulation site in psychiatry, making it particularly important to monitor tolerability and carefully document potential side effects, including common discomforts such as headache or fatigue. We however expect that adverse effects such as pain or discomfort from nerve stimulation under the skin due to rTMS will be milder compared to the stimulation of frontal regions, which are more richly innervated.

Third, stakeholder attitudes may also influence feasibility. Qualitative studies indicate that patients, family members, and clinicians can all express reservations, though for different reasons. Family members often highlight concerns about autonomy, identity, or the perceived intrusiveness of brain stimulation, while clinicians sometimes emphasize uncertainties regarding efficacy, logistical demands, or the potential to disrupt therapeutic engagement. These perspectives suggest that transparent communication with both relatives and treating teams is essential, not only to sustain participation but also to contextualize possible benefits and risks within ongoing care (Dalton et al., 2021).

Fourth, methodological risks also warrant consideration. Achieving a convincing sham condition remains challenging in TMS trials, even with the use of advanced double-coil systems, as subtle differences in scalp sensations or auditory cues may compromise blinding (Duecker and Sack, 2015), with potential resentful demoralization that could jeopardize compliance, or compensatory rivalry that could hinder the detection of treatment effects (McCambridge et al., 2014). Moreover, the mere possibility of being randomized to the sham arm can reduce willingness to participate and heighten concerns about the treatment, particularly in a population where ambivalence toward intervention is already common. For these reasons, assessing blinding integrity and carefully documenting reasons for refusal or discontinuation will be crucial for interpreting trial outcomes and for informing the design of future studies.

In summary, this protocol combines a neurobiologically informed stimulation strategy with outcome measures that capture both explicit and implicit dimensions of AN, while addressing the practical and methodological challenges inherent to this population. The findings are expected to inform not only the feasibility of posterior parietal non-invasive stimulation in treating AN, but also its potential role within the broader landscape of precision interventions for eating disorders.
